##### 4.1.1 Inclusion Criteria

*A subject must meet all of the following criteria:*

1. 18 to 70 years old

2. Available for clinical follow-up through Study Week 40 for Groups 1-2 and through Study Week 64 for Groups 3-6
3. Able and willing to complete the informed consent process
4. Willing to donate blood for sample storage to be used for future research
5. Physical examination and laboratory results without clinically significant findings and a Body Mass Index (BMI)  $\leq 40$  within the 70 days prior to enrollment
6. Has not yet received the current year (2012/13) influenza vaccine prior to enrollment and agrees to receive seasonal influenza vaccines during study participation only from the study site

*Laboratory Criteria within 70 days prior to enrollment:*

7. Hemoglobin within institutional normal limits
8. White blood cells either within institutional normal range or accompanied by site physician approval as consistent with healthy adult status
9. Platelets = 125,000 – 500,000/mm^3
10. Alanine aminotransferase (ALT)  $\leq 2.5$  x upper limit of normal (ULN)
11. Serum creatinine  $\leq 1$  x ULN based on site institutional normal range

*Criteria applicable to women of childbearing potential:*

12. Negative human chorionic gonadotropin ( $\beta$ -HCG) pregnancy test (urine or serum) on day of enrollment
13. Agree to use an effective means of birth control from 21 days prior to enrollment through 3 weeks after the second study vaccination

**4.1.2 Exclusion Criteria**

*A subject will be excluded if one or more of the following conditions apply:*

*Women Specific:*

1. Breast-feeding or planning to become pregnant while participating in the study

*Subject has received any of the following substances:*

2. More than 10 days of systemic immunosuppressive medications or cytotoxic medications within the 12 weeks prior to enrollment or any within the 14 days prior to enrollment

3. Blood products within 16 weeks prior to enrollment
4. Immunoglobulin within 8 weeks prior to enrollment
5. Investigational research agents within 28 days (4 weeks) prior to enrollment or planning to receive investigational products while on the study.
6. Allergy treatment with antigen injections, unless on maintenance schedule and allergy shots could be staggered with the study vaccinations, within 14 days (2 weeks) prior to enrollment
7. Current anti-TB prophylaxis or therapy

*Subject has a history of any of the following clinically significant conditions:*

8. Contraindication to receiving an FDA-approved seasonal influenza vaccination
9. Serious reactions to vaccines that preclude receipt of study vaccinations, as determined by the site investigator
10. Hereditary angioedema (HAE), acquired angioedema (AAE), or idiopathic forms of angioedema
11. Asthma that is severe, unstable or required emergent care, urgent care, hospitalization or intubation during the previous two years or that is expected to require the use of oral, intravenous or high dose inhaled corticosteroids
12. Diabetes mellitus type I
13. Thyroid disease that is not well-controlled
14. Generalized idiopathic urticaria within the 1 year prior to enrollment
15. Hypertension that is not well controlled
16. Bleeding disorder diagnosed by a doctor (e.g. factor deficiency, coagulopathy, or platelet disorder requiring special precautions), or significant bruising or bleeding difficulties with IM injections or blood draws, or use of blood thinners such as Coumadin or Plavix®
17. Malignancy that is active or treated malignancy for which there is not *reasonable* assurance of sustained cure or malignancy that is likely to recur during the period of the study

18. Seizure disorder other than: 1) febrile seizures, 2) seizures secondary to alcohol withdrawal more than 3 years ago, or 3) seizures for which no treatment has been required within the 3 years prior to enrollment
19. Asplenia, functional asplenia or any condition resulting in the absence or removal of the spleen
20. Guillain-Barré Syndrome
21. Psychiatric condition that precludes compliance with the protocol; past or present psychoses; disorder requiring lithium; or within 5 years prior to enrollment, a history of suicide plan or attempt
22. Any medical, psychiatric, or other condition that, in the judgment of the investigator, is a contraindication to protocol participation or impairs ability to give informed consent

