In this study, we are evaluating the safety and immunogenicity of same season and sequential season vaccination schedules. The same season regimens (2012/13 prime and boost with a 16 week interval) consist of HA DNA prime with ATIV boost -- or -- HA DNA prime with TIV boost; the active comparator for these regimens will be ATIV or TIV alone because this is the standard for adult influenza vaccination within a single season. The sequential season regimens (2012/13 prime and 2013/14 boost with a 44 week interval) consist of concurrent administration (in different arms) of HA DNA and ATIV prime with ATIV boost -- or -- HA DNA and TIV prime with TIV boost; the active comparator for these regimens will be ATIV followed by ATIV boost or TIV followed by TIV boost, also at a 44 week interval, because this is a vaccination pattern consistent with sequential season vaccinations. Evaluation of these investigational schedules and active comparator schedules will inform development of novel influenza vaccine strategies that may offer improved and cross-protective immunity against antigenically diverse influenza strains.

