## **1.2 RATIONALE FOR SEASONAL INFLUENZA DNA VACCINE PRIME FOLLOWED BY TIV BOOST**

DNA vaccines have the potential to be manufactured rapidly. They are known to induce balanced immune responses that induce both humoral and cellular immunity. The experience to date with HA DNA vaccines warrants continued investigation. One approach to improving immunity to influenza would be to prime the population with an HA DNA vaccine early in the year and to boost with TIV when the influenza season begins in order to provide better immunogenicity, especially to novel influenza strains. This may be a useful strategy for the older adult and pediatric populations for which the TIV vaccine alone has a lower efficacy than in young adults. In previous studies, the VRC has found that antibody responses are higher after the boost when there is a long prime-boost interval, such as 6 months compared to a short interval, such as 1 month [4]. For this reason, single dose DNA priming schedules with a long interval between prime and boost are being evaluated towards the goal of an influenza vaccination strategy with improved immunogenicity.

A DNA vaccine may also elicit CD8 T cell responses to conserved HA epitopes that may afford some cross-protection [24-26]. It has been also suggested that T cell responses are the important correlates of influenza vaccine protection, especially in the elderly populations immunized with the seasonal flu vaccines [27, 28].

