There was no severe local or systemic reactogenicity. Mild local reactogenicity was reported in a majority of the H5 DNA vaccine recipients (83%) while 2% reported moderate local reactogenicity. The majority of the H5 DNA vaccine recipients reported no systemic reactogenicity; 23% reported mild and 5% reported moderate systemic reactogenicity. No SAE were reported following the H5 DNA vaccinations; there was one SAE reported in the follow-up period through 48 weeks: multiple injuries unrelated to study participation in the period after the H5N1 booster. All adverse events following H5 DNA injection were mild (Grade 1) or moderate (Grade 2) except for one severe (Grade 3) case of gastroenteritis with onset 15 days after receiving H5 DNA vaccination, which was assessed as unrelated to vaccine.

In assessing immunogenicity of H5 DNA vaccine followed by MIV, a single H5 DNA vaccine prime followed by a single MIV boost at short intervals (4-8 weeks) did not significantly improve HAI titers over levels achieved with inactivated vaccine alone. However, a single H5 DNA 4 mg vaccination prime significantly improved HAI responses when the interval to the inactivated vaccine boost was 16-24 weeks, as compared with receiving two doses of the inactivated vaccine at the same interval [4]. Therefore, a single dose of DNA priming may be sufficient to increase the magnitude and breadth of HA-specific antibody responses.

Seasonal HA DNA vaccine studies: Specifically, with regard to seasonal influenza vaccines developed by the VRC/NIAID/NIH, VRC-FLUDNA047-00-VP, VRC-FLUDNA056-00-VP, VRC-FLUDNA061-00-VP (BB-IND 13939 and BB-IND 14093) and VRC-FLUDNA063-00-VP (BB-IND 15062) are season-specific 3-plasmid DNA vaccines; while VRC-FLUDNA057-00-VP (BB-IND 14093) is a single plasmid H1 DNA based on the 2009 pandemic H1N1 influenza virus. **Table 1-2** shows the composition of these investigational influenza DNA vaccines.

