VRC 701 includes 131 subjects (18-70 years) enrolled in Jan-Feb 2012 who were randomized to receive a blinded injection of 2011/12 HA DNA vaccine or placebo, which will be followed by a boost with the 2012/13 TIV in Fall 2012. Interim data as of February 27, 2012 indicates that the (still blinded) prime injections were well tolerated. Solicited adverse events (reactogenicity) were collected for 7 days. For local reactogenicity, 41.2% reported none, 55% reported mild and 3.8% reported moderate as the maximum severity. For systemic reactogenicity, 76.3% reported

none, 21.4% reported mild and 2.3% reported moderate as the maximum severity. Pain at the injection site was the most frequently reported solicited AE (55% of subjects), with headache reported by 18.2% and all other solicited symptoms each reported by fewer than 10% of subjects. Fever was the least frequently reported symptom and was recorded by 1 subject (0.8%). There have been no SAEs. At least one unsolicited adverse event has been reported by 34 (26%) subjects. All were mild or moderate except for one report of a severe vasovagal reaction, which was not associated with loss of consciousness but was considered grade 3 because the systolic blood pressure was 68. Mild bruising at the injection site was the most frequently reported (6.1%). Mild macular rash was reported by 1 subject at the injection site (0.8%) and at other than injection site by 2 subjects (1.5%) within the first week after injection. No subjects have discontinued the study to date.

Summary of HA DNA safety and immunogenicity: The safety data for the VRC HA DNA vaccine trials to date shows that these vaccines were well tolerated. No severe local or systemic reactogenicity occurred nor were there any serious adverse events related to vaccine. The pattern of local and systemic reactogenicity appears to be generally mild and similar across the studies, independent of the antigens encoded by the HA DNA constructs included in any one vaccine.

Regarding immunogenicity, seasonal HA DNA priming did not significantly improve HAI response compared to TIV alone with the boost administered at a 3-4 week interval. However, data from studies of the H5 DNA vaccine using various H5N1 inactivated vaccine (MIV) boost intervals show that a longer interval is associated with a higher magnitude of immune response [4].

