### **8.5.2 Risks of the DNA Vaccine:**

This is one of the two studies in humans of the trivalent seasonal HA DNA vaccine, VRC-FLUDNA063-00-VP. The H1 DNA plasmid previously has been administered alone and as part of another HA DNA vaccine. The risks noted are based on risks from the earlier DNA vaccine studies of similar influenza DNA vaccines, as well as risks of vaccines in general and results of previous studies with other investigational DNA vaccines.

Subjects may exhibit general signs and symptoms associated with administration of a vaccine injection, including fever, chills, rash, aches and pains, nausea, headache, dizziness and fatigue. These side effects, when they occur, are generally short term, mild to moderate severity, and usually do not require treatment.

In previous VRC DNA vaccine studies, placebo and vaccine recipients were noted to have occasional asymptomatic and self-limited changes in the laboratory tests routinely followed during the clinical trial. Urticaria has been reported as an infrequent adverse event possibly related to DNA vaccines.

Investigational DNA vaccines administered via Biojector have been associated with mild skin lesions (0.5-1.0 cm diameter) at the vaccination site. In these cases, a small scab formed within 1-2 weeks after immunization and came off after a few days. The skin healed without treatment within a few weeks. One skin biopsy was obtained on Day 6 post vaccination. It showed subcutaneous and dermal perivascular lymphocytic inflammation. There were rare eosinophils and rare giant cells noted, and the infiltrate was composed entirely of CD3 positive cells. It included both CD4+ and CD8+ T cells. The process appears to be primarily a subcutaneous inflammatory response to vaccination with cutaneous manifestations.

There may be other unknown side effects.

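### The 28-day washout does not keep earlier HA DNA recipients out of the ATIV-alone and TIV-alone comparators: a small eligibility gap, mainly for H1

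*Protocol*

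**What the plan says.** Protocol 4.1.2, exclusion 5 rules out anyone with "Investigational research agents within 28 days (4 weeks) prior to enrollment or planning to receive investigational products while on the study". It is the only criterion on earlier investigational agents. None of the 13 inclusion or 22 exclusion criteria mentions earlier HA DNA vaccination or an earlier injection in VRC 703. Inclusion 6 (4.1.1) sets two further conditions. The first is that a subject "Has not yet received the current year (2012/13) influenza vaccine prior to enrollment". The second concerns doses given later, during the trial: the subject "agrees to receive seasonal influenza vaccines during study participation only from the study site".

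The primary immunogenicity objective (3.1, 6.4.3) compares Group 1 after its ATIV boost with Group 3 after its first ATIV injection, and Group 2 with Group 4 in the same way for TIV. On the same-season regimens, section 1 states that "the active comparator for these regimens will be ATIV or TIV alone". Section 6.5.4 analyses all enrolled subjects as randomized.

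On how long a prime lasts, section 1.2 reports that "antibody responses are higher after the boost when there is a long prime-boost interval", and section 1.4.2 that "a single H5 DNA 4 mg vaccination prime significantly improved HAI responses when the interval to the inactivated vaccine boost was 16-24 weeks". The same section says that a boost 4 to 8 weeks after the prime gave no significant gain.

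On earlier exposure to this product's components, section 8.5.2 says "The H1 DNA plasmid previously has been administered alone and as part of another HA DNA vaccine".

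**The concern.** The trial rests on the premise that one DNA prime alters the response to an inactivated vaccine given months later. A 28-day look-back may suit other agents, but it runs out before the interval at which the protocol expects this prime to show its effect. A person primed earlier and then randomized to Group 3 or 4 would meet every written criterion, yet would not supply an unprimed response to ATIV or TIV.

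What is at stake is the meaning of the comparator in the primary contrast. Primed people entering Groups 1 and 2 do not offset this, because those groups receive a DNA prime anyway. The exposure could also go unseen. Section 4.2.6 provides for recording current medications at enrollment and vaccinations received during participation, and neither captures a DNA vaccine given in an earlier trial.

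**Working it through.** **1. Who could enter, by the text.**

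| Route | What the Protocol gives | What narrows it |
|---|---|---|
| VRC 308 | 20 adults given the H1 plasmid VRC-9328 (1.4.2, Table 1-2) | 18 also took the inactivated H1N1 boost, so 20 − 18 = 2 did not |
| VRC 701 | "VRC 701 includes 131 subjects (18-70 years) enrolled in Jan-Feb 2012", randomized to HA DNA or placebo (split not stated); same H1 plasmid | TIV boost due in fall 2012; inclusion 6 bars a subject who has had it and conflicts with a pending one; no discontinuations by 27 February 2012 |
| VRC 703 Groups 1 and 2 | Primed from August 2012; Groups 3 to 6 enrol from October (6.5.6) | Must leave before the boost and be randomized a second time, which no text foresees or forbids |

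The remaining route through VRC 701 is a subject who forgoes the boost.

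**2. Intervals from prime to the Group 3/4 injection in October or November 2012.**
- VRC 701: from 29 February to 1 October is 215 days (31 weeks); from 1 January to 30 November is 334 days (48 weeks). All of this exceeds 16 weeks.
- Group 1/2 leaver: from 31 August to 1 October is 31 days (4.4 weeks); from 1 August to 30 November is 121 days (17 weeks). All of this exceeds 28 days, but much of it is below 16 weeks.

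**3. Strain overlap (Table 1-2).** VRC-9328 (H1) is in the VRC 308, VRC 701 and present products. The present H3 plasmid (VRC-3027) and B plasmid (VRC-2722) are in no earlier adult product. Apart from a Group 1/2 leaver, a plasmid-matched prime can therefore affect only H1.

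**4. Reproducing the plan's power.** Method: two-sided Fisher's exact test at 5%, with power summed over the two binomial distributions, N = 55 per group. Results against Table 6-3: 0.4 vs 0.7 gives 84.6% (stated 85); 0.5 vs 0.8 gives 89.1% (stated 89); 0.6 vs 0.9 gives 94.8% (stated 95); 0.7 vs 0.9 gives 68.2% (stated 68). For Table 6-4, 0.50 vs 0.77 gives 79.9% (stated 80). The tables are sound.

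**5. Effect of k primed subjects in a comparator group.** Worst-case assumption: each responds at the prime-boost rate p1 instead of the comparator rate p0, and the prime-boost group is unchanged. Then

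p0* = p0 + (p1 − p0) × k/55.

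For 0.50 vs 0.77 with k = 3: p0* = 0.50 + 0.27 × 3/55 = 0.5147, and the true difference falls from 0.27 to 0.2553.

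| True rates | k = 0 | k = 1 | k = 3 | Loss at 1 and 3 |
|---|---|---|---|---|
| 0.50 vs 0.77 | 79.9% | 78.4% | 75.3% | 1.5 and 4.6 |
| 0.4 vs 0.7 | 84.6% | 83.2% | 80.1% | 1.4 and 4.5 |
| 0.5 vs 0.8 | 89.1% | 87.9% | 85.4% | 1.2 and 3.7 |
| 0.6 vs 0.9 | 94.8% | 94.1% | 92.5% | 0.7 and 2.3 |

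**6. What k implies.** The 220 later subjects are allocated equally to four groups, so k per comparator group corresponds to about 4k earlier recipients among the 220: 4 for k = 1 and 12 for k = 3.

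**7. Direction.** For geometric mean titer, a primed comparator subject who responds more strongly narrows the contrast. For seroconversion, 6.3.2 requires a four-fold rise when the baseline titer is at least 1:40. Earlier vaccination that raised the baseline could make seroconversion less likely, which would lower the comparator rate and widen the contrast.

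**The case against.** The strongest reply is that the route is narrow and the harm conjectural. The documents give no count of likely repeat volunteers and do not show that VRC 703 sites overlap with earlier trial sites. Inclusion 6 largely closes the VRC 701 route, and almost all VRC 308 subjects were already boosted. Sections 6.4 and 6.5.6 speak of a first 110 and then 220 further subjects, which reads as 330 different people. Section 1.5 expects these adults to carry pre-existing influenza immunity in any case, and section 6.4 disclaims a formal superiority or non-inferiority test. All of this stands, and it bounds the size. It does not supply the missing criterion.

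A reader might go further and count every earlier VRC influenza DNA recipient as a contaminating candidate: 74 + 99 for H5, 66 in VRC 307 and 309, and 20 in VRC 308, or 259, plus the DNA arm of VRC 701. The documents do not support that. H5 is not in the 2012/13 vaccine. The VRC 307 and 309 products used other plasmids for all three strains, on a 3- to 4-week boost schedule at which section 1.4.2 reports no significant HAI gain.

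A reader might also infer that the primary contrast is in fact diluted. That would need a known share of primed subjects and a known direction, and the documents give neither.

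**Conclusion.** The gap is real and of low severity. Exclusion 5 does not match the duration of effect on which the trial is built, and the criteria as written admit a previously primed person to Group 3 or 4. One to three such people per comparator group would cost about 1.5 to 4.5 points of power at 0.50 vs 0.77 or 0.4 vs 0.7, and less at 0.5 vs 0.8 or 0.6 vs 0.9. These figures rest on an assumed count and on every such subject responding at the full prime-boost rate, so they are upper limits for those counts. The exposure concerns mainly the H1 comparison. The bias may run either way for seroconversion. Tables 6-3 and 6-4 need no change.

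**What to change.** Add one line to 4.1.2 that excludes anyone who has at any time received an investigational influenza HA DNA vaccine or who has already had a study injection in VRC 703. Add one matching question at screening; the pre-enrollment interview in 4.2.1 already covers self-reported history and can carry it. Keep the 28-day rule for other investigational agents.

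The cost is the loss of a few willing repeat volunteers. If that is unwelcome, the minimum is to record earlier influenza DNA vaccination at screening and to prespecify a sensitivity analysis of the primary comparisons without those subjects. If this history is not collected, the exposure cannot be assessed afterwards.

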## 4.2 STUDY SCHEDULES

The study schema is shown in Table 4.1 and the study schedules that apply to study Groups are in **Appendix III**. Schedule A applies to Groups 1 and 2, while Schedule B applies to Groups 3, 4, 5 and 6. After Day 0, deviations from the visit windows in completing study visits are discouraged and will be recorded as protocol deviations, but are permitted, at the discretion of the Investigator of Record (IoR) or designee in the interest of obtaining subject safety and immunogenicity evaluations following study vaccinations.

During or following any visit, if there is any concern about the well-being of the subject, the clinical study site will conduct appropriate medical evaluations by history, physical, laboratory or other indicated testing.

### 4.2.1 Pre-enrollment

Potential study subjects who verbally agree to discuss their medical history may complete an interview questionnaire by telephone or in person that covers protocol inclusion and exclusion criteria that are based on key self-reported history information to identify potential study volunteers.

### 4.2.2 Screening Visit(s)

Screening for this study may be completed through a general screening protocol after signing consent to be screened or screening consent may be incorporated into a VRC 703-specific consent form. A screening segment for the study will be included in data collection to provide information on reasons for non-enrollment. Evaluations will be done according to eligibility criteria and clinical assessment at screening. Screening evaluations for specific eligibility criteria must be completed within the time interval specified prior to enrollment, but may be repeated as needed to confirm eligibility. Storage samples of peripheral blood mononuclear cells (PBMCs) and serum collected during screening may be used for assay validation and site proficiency testing. As part of the screening process, an Assessment of Understanding (AoU) should be completed and incorrect answers will be explained to the subject.

